#### Intervention Group

All participants in the intervention group received the 2-day psychotherapy training program and were given a hard copy of the program booklet at recruitment. Additionally, supervision-based group meetings were held during the follow-ups at weeks 1, 2, 4, and 8, with each meeting lasting approximately 2 hours. During these follow-up meetings, instructors—including psychotherapists and psychiatrists—were available to answer any psychotherapy-related questions, encourage participants to practice psychological interventions, and provide further information to support the clinical application of psychotherapy.

### Outcomes and Outcome Measures

#### Primary Outcome

Trainees’ psychotherapy knowledge was assessed by participants using an 11-point scale (ranging from 0 to 10) before and after the 8-week period (Table 2). At baseline, 160 participants completed the self-reported psychotherapy knowledge questionnaire, and the results indicated a high internal consistency coefficient (Cronbach α) of 0.980 for the scores across the 17 items.

**Table 2 table2:** Knowledge about psychotherapy.^a^

Variables	Measures (0-10)
Overview of psychotherapy	
Supportive psychotherapy techniques	
Overview of cognitive behavioral therapy	
Beck’s cognitive therapy	
Identify automatic thinking and do cognitive conceptualization	
Cognitive conceptualization	
Evaluation of automatic thinking	
Reconstruction techniques for automated thinking1: Socratic questioning	
Reconstruction techniques for automated thinking2: pie charts, continuous spectrum, cost-benefit analysis, behavioral experiments	
Challenge automatic thinking	
Social skill training	
Problem-solving	
Behavioral therapy theory and behavioral conceptualization	
Behavioral activation	
Relaxation training	
Exposure therapy	
Competency structure of psychotherapists and the growth path of cognitive behavioral therapy therapists	

^a^This is the assessment of participants’ knowledge about psychotherapy. Each item was rated on a 0-10 scale, where 10 means “knowing very well.”

#### Secondary Outcomes

##### Training Program Acceptability

Program acceptability in the intervention group was measured using questions designed to assess acceptability, as detailed in Table 3.

**Table 3 table3:** Questions for assessing the psychotherapy training program acceptability.^a^

Category and questions		Rating
**General**		
	Overall rating of the program	5=like very much; 4=like somewhat; 3=neutral; 2=dislike somewhat; 1=very dislike; 5=very likely
**Appraisal**		
	Appraisal of the program—the likelihood of applying the program for patients Appraisal of the program—the likelihood of recommending the program to other medical students or other health care providers	5=very likely; 4=somewhat likely; 3=neutral; 2=unlikely; 1=not at all likely
**Acceptability**		
	I would have been able to help patients to deal with mental problems with the program The program made it easier to communicate and help patients during clinical work The program disrupted my daily schedule The program is easy to understand	5=strongly agree; 4=agree; 3=neutral; 2=disagree; 1=strongly disagree
**Frequency**		
	Frequency of using psychotherapy	1=almost never; 2=sometimes; 3=always

^a^This is the rating of the training acceptability assessment. The last item, “Frequency of using psychotherapy,” was rated on a 1-3 Likert scale, where 3 indicates “always.”

##### Utilization of Psychotherapy

The utilization rate of psychotherapy interventions for patients during the 8 weeks of follow-up was assessed using items from Table 4.

**Table 4 table4:** The utilization rate of psychotherapy.^a^

Variables	Measures (0-10)
Supportive psychotherapy techniques	
Social skill	
Problem-solving skill	
Behavioral activation	
Relaxation training	
Exposure therapy	

^a^This is the assessment of participants’ utilization rate of psychotherapy. Each item was rated on a 0-10 scale, where 10 means maximum utilization and 0 means minimum utilization.

##### Self-Reported Self-Efficacy and Self-Reported Motivation

Self-efficacy and motivation were measured using a visual analog scale on a 10-cm line, representing a continuum from “no self-efficacy or motivation” to “the strongest self-efficacy or motivation” (Table 5).

**Table 5 table5:** Self-reported self-efficacy and motivation of psychotherapy.^a^

Variables		Visual analog scale
**Self-reported self-efficacy**		
	Confidence in practicing psychotherapy	
	Confidence in practicing supportive psychotherapy	
	Confidence in practicing cognitive behavioral therapy	
**Self-reported** **m** **otivation**		
	Willingness or motivation to practice psychotherapy	
	Willingness or motivation to practice supportive psychotherapy	
	Willingness or motivation to practice cognitive behavioral therapy	

^a^This is the assessment of participants’ self-reported self-efficacy and self-reported motivation. Each item was measured by the visual analog scale on a 10-cm line that represents a continuum between “no self-efficacy or motivation” and “the strongest self-efficacy or motivation.

All secondary outcomes were reported as mean values. According to the baseline measurements of our study, 160 participants evaluated their psychotherapy utilization, confidence, and motivation using self-reported questionnaires. The internal consistency coefficients (Cronbach α) for these 3 questionnaires were 0.950, 0.961, and 0.936, respectively.

### Procedures

Figure 1 and Table 1 summarize the schedule for enrollment and posttraining assessments. Participants were evaluated at baseline (0 weeks), before and after receiving the intervention training, and at 8 weeks after training. They were also asked to maintain a daily log of their utilization of the psychotherapy training program, which included activities such as providing emotional support and teaching patients breathing techniques for stress relief. Reminders were sent to participants who did not complete the 8-week posttraining questionnaires.

### Withdrawal From the Program

All participants were free to withdraw from the trial at any time without needing to provide a reason. Following the intention-to-treat principle [15], participants who did not respond to the 8-week posttraining assessment were retained in the analysis according to the group to which they were randomized, regardless of whether they received the intervention. Participants who withdrew were excluded from the analysis, and their reasons for withdrawal were recorded. A complete case analysis was conducted, excluding any participants who withdrew at the posttraining assessment point.

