**Results:**

A total of 160 participants were recruited and randomized between January 4 and 12, 2024. Baseline assessments were conducted from January 28 to February 1, 2024. The psychotherapy training program for the intervention group took place on February 3 and 4, 2024. Posttraining assessments were conducted starting April 1, 2024. Due to withdrawals, incomplete surveys, and data loss, we had a total of 113 participants: 57 in the intervention group and 56 in the control group. The amount of data varied across measures. The data analysis was finished in August 2024.

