### Data Analysis

All data were automatically collected via WenJuanXing through a WeChat-based link. The data were downloaded from the WenJuanXing database into a user-specific Excel file. This study did not include interim analyses; data were analyzed only after all had been collected. The trial statistician blinded the intervention assignment in the data using R software (R Foundation for Statistical Computing) and SPSS (2013 release; IBM Corp.).

The primary hypothesis was that, compared with the control intervention, the intervention group receiving the psychotherapy teaching program would significantly gain more knowledge about psychotherapy after training. We also hypothesized that the program would lead to increased utilization of psychotherapy and be associated with improvements in knowledge. The third hypothesis posited that trainees’ self-reported self-efficacy and motivation to apply psychotherapy in clinical practice would increase significantly.

Descriptive statistics were used to assess demographic and psychotherapy-related characteristics at baseline. Following normality and homogeneity of variance tests, ANCOVA was used to analyze the primary outcomes. In the ANCOVA model, the dependent variable was the change in the knowledge score. The fixed factor was the group (intervention group or control group), while the covariates included the mean score of psychotherapy knowledge at baseline and years of psychotherapy experience. Pearson correlations and regression analysis (both linear and binary regression models) were used to explore factors associated with the knowledge score at baseline and to assess the increase in psychotherapy utilization in both the intervention and control groups. The secondary outcomes—participants’ psychotherapy utilization, confidence, and motivation—will also be analyzed in the same manner as knowledge.

A complete case analysis was performed, excluding any participants with missing information on the posttraining assessment. Additionally, a sensitivity analysis of the missing data was conducted to determine whether the missingness is random. Demographic information and scores for psychotherapy knowledge, utilization, confidence, and motivation at baseline were compared between the complete data group and the missing data group. All tests were 2-tailed, with a significance level set at *P*<.05.

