## Results

This study recruited 160 participants from January 4 to January 12, 2024. The 2-day training program took place on February 3 and February 4, 2024, and the posttraining assessment was completed on April 1, 2024. Due to withdrawals, incomplete surveys, and data loss, we had a total of 113 participants: 57 in the intervention group and 56 in the control group. The amount of data varies for each measure. Data analysis was completed in August 2024. The results will be published in peer-reviewed journals. If found to be effective, the psychotherapy training program and the accompanying program booklet will be made freely available to the public by the end of the trial.

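### The plan invokes intention-to-treat with week-8 non-responders retained, but its exclusion rules make the primary analysis a completer analysis (113 of 160 overall), so the intention-to-treat description is wrong

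*Protocol article*

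**What the plan says.** All statements come from the Protocol article.

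- **Withdrawal From the Program**, on intention-to-treat: "participants who did not respond to the 8-week posttraining assessment were retained in the analysis according to the group to which they were randomized", whether or not they received the intervention.
- **Same paragraph**, on withdrawals: "Participants who withdrew were excluded from the analysis, and their reasons for withdrawal were recorded".
- **Same paragraph**, closing sentence: "A complete case analysis was conducted, excluding any participants who withdrew at the posttraining assessment point".
- **Data Analysis**: "A complete case analysis was performed, excluding any participants with missing information on the posttraining assessment".
- **Data Analysis**, primary model: ANCOVA on the change in knowledge score, with group as factor and baseline knowledge and years of experience as covariates.
- **Data Analysis**, missing data: "a sensitivity analysis of the missing data was conducted to determine whether the missingness is random". This is done by comparing the baseline data of those with complete and those with missing data.
- **Abstract, Results**: "A total of 160 participants were recruited and randomized between January 4 and 12, 2024".
- **Results**: "we had a total of 113 participants: 57 in the intervention group and 56 in the control group", and "The amount of data varies for each measure".

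**The concern.** A participant who does not answer at week 8 is kept by one rule and removed by another. A reader therefore cannot tell which population the primary test covers. The intention-to-treat wording suggests protection against attrition bias that a completer analysis does not give. Randomisation makes the two arms comparable as allocated. Once people are selected on whether they answered at week 8, that comparability has to be assumed.

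The loss is large enough to matter: more than a quarter of those randomised, and above the 25% per arm allowed for in Sample Size and Power Calculation. Because the amount of data differs by measure, each outcome may also rest on a different subset.

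**Working it through.** **1. Can both rules hold?** Take a person who was randomised, did not formally withdraw and did not answer at week 8.

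| Rule | Result for this person |
|---|---|
| Withdrawal From the Program, intention-to-treat sentence | Kept, in the randomised arm |
| Withdrawal From the Program, two sentences on withdrawals | Not removed by the letter, as the person did not withdraw, although the second calls the analysis complete case |
| Data Analysis, complete case sentence | Removed, as post-training information is missing |

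The firm conflict is between the two sections. The primary model confirms it. Table 1 schedules knowledge at baseline and 8 weeks only, and the dependent variable is the difference between them. (Procedures could be read as adding an assessment directly after training, but Table 1 lists none.) A non-responder has no value to enter, and the article names no way to supply one. The rule that can be carried out is the complete case rule.

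**2. How many are left out?**

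- The article's count: 57 + 56 = 113, which agrees.
- Share with data: 113/160 = 70.6%. Left out: 160 − 113 = 47, and 47/160 = 29.4%.
- By arm, assuming exactly 80 randomised to each (the article gives 80 as a target): intervention 80 − 57 = 23 (28.75%), control 80 − 56 = 24 (30.0%).
- The 113 is an overall count. The number for the knowledge score alone is not given.

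**3. What could this do to the effect?** Assumptions, none of them from the article's data: a completer effect of 0.50 SD (this matches the planning value f = 0.25, as d = 2f for two equal arms), 80 per arm, and control non-responders no different from control responders. Let e be the effect in intervention non-responders.

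All-randomised effect = 0.50 × 57/80 + e × 23/80

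| e (SD) | Calculation | All-randomised effect (SD) |
|---|---|---|
| 0 | 0.356 + 0 | 0.36 |
| 0.25 | 0.356 + 0.072 | 0.43 |
| 0.50 | 0.356 + 0.144 | 0.50 |

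**4. Does the planned sensitivity analysis settle it?** No. Comparing baseline data can show whether missingness is related to measured baseline variables. It cannot show whether it depends on the unseen week-8 score, and it yields no second estimate of the effect.

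**5. Would imputation alone settle it?** Not if disengaged trainees gained less. Imputation by arm under missing-at-random fills the 23 with gains like those of intervention responders with the same predictors. Unless the predictors explain the smaller gain, the expected result is 0.50 × 57/80 + 0.50 × 23/80 = 0.50, whatever e really is.

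**The case against.** The strongest defence has four parts.

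*The paragraph separates two kinds of people.* Non-responders are kept and withdrawals are dropped, so the paragraph could be consistent with itself. That is a fair reading of the paragraph alone. It fails against Data Analysis, which excludes on missing information and not on withdrawal.

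*The article is open about what was done.* Complete case analysis is stated in both sections, and the 113 appears in the Abstract and in Results. This stands. A reader might infer that a result has been published under an intention-to-treat label. The article reports no effect estimate, so the documents do not support that. The fault lies in how the plan describes its analysis.

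*Inflation is not shown.* A reader might also infer that the completer effect is too large, say 0.50 SD where the truth is 0.36 SD. The documents do not support this either. The 0.36 requires no effect at all in intervention non-responders, which is close to the extreme. Losses are nearly equal between arms, and the article attributes them partly to incomplete surveys and lost data. The control losses cannot be disengagement from a course that controls had not yet received. Equal loss does not rule out bias, but it leaves its direction open.

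*A separate analysis plan may give the method for keeping non-responders.* It may, and the lack of a named method is not counted here as a fault of its own. It would not remove the explicit exclusion in Data Analysis, which still contradicts the retention sentence.

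**Conclusion.** The point holds as a contradiction in the text. The plan claims intention-to-treat with non-responders retained, while the analysis that can be run is a completer analysis covering 113 of 160 overall (70.6%, with 29.4% left out). The intention-to-treat description is therefore wrong. These shares need only the article's counts; the split by arm assumes 80 per arm, and the number for the primary outcome may differ from 113.

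The effect on the result is unknown in size and direction. The range of 0.36 to 0.50 SD illustrates what is at stake under an assumed completer effect of 0.50 SD. It does not estimate the bias.

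**What to change.** Reconcile Withdrawal From the Program with Data Analysis. Three sentences exclude people (two in the first section, one in the second), and all three must agree with whichever rule is kept. Then choose one of two routes.

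- **(a) Complete case stays primary.** Delete the intention-to-treat claim, call the analysis complete case, give the number analysed for each outcome, and limit the conclusion to week-8 responders.
- **(b) All 160 are analysed as randomised.** Impute week-8 scores by multiple imputation within each arm, using the baseline scores for knowledge, utilization, self-efficacy and motivation, the demographic and professional variables, and any week-8 measure the person did complete. Keep complete case ANCOVA as secondary.

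Under either route, add a delta-adjusted or reference-based (control-arm) sensitivity analysis over a stated range, for example from no effect in intervention non-responders up to the completer effect. This is the part that addresses trainees who disengaged and gained less, which imputation by arm does not.

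Cost: route (a) is wording, plus the programming of the sensitivity analysis. Route (b) adds a few hours of programming. No new data are needed, as the article reports baseline questionnaires from 160 participants. Data analysis was completed in August 2024, so any change must be declared as post hoc when the results are published.

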### Data Analysis

All data were automatically collected via WenJuanXing through a WeChat-based link. The data were downloaded from the WenJuanXing database into a user-specific Excel file. This study did not include interim analyses; data were analyzed only after all had been collected. The trial statistician blinded the intervention assignment in the data using R software (R Foundation for Statistical Computing) and SPSS (2013 release; IBM Corp.).

The primary hypothesis was that, compared with the control intervention, the intervention group receiving the psychotherapy teaching program would significantly gain more knowledge about psychotherapy after training. We also hypothesized that the program would lead to increased utilization of psychotherapy and be associated with improvements in knowledge. The third hypothesis posited that trainees’ self-reported self-efficacy and motivation to apply psychotherapy in clinical practice would increase significantly.

Descriptive statistics were used to assess demographic and psychotherapy-related characteristics at baseline. Following normality and homogeneity of variance tests, ANCOVA was used to analyze the primary outcomes. In the ANCOVA model, the dependent variable was the change in the knowledge score. The fixed factor was the group (intervention group or control group), while the covariates included the mean score of psychotherapy knowledge at baseline and years of psychotherapy experience. Pearson correlations and regression analysis (both linear and binary regression models) were used to explore factors associated with the knowledge score at baseline and to assess the increase in psychotherapy utilization in both the intervention and control groups. The secondary outcomes—participants’ psychotherapy utilization, confidence, and motivation—will also be analyzed in the same manner as knowledge.

A complete case analysis was performed, excluding any participants with missing information on the posttraining assessment. Additionally, a sensitivity analysis of the missing data was conducted to determine whether the missingness is random. Demographic information and scores for psychotherapy knowledge, utilization, confidence, and motivation at baseline were compared between the complete data group and the missing data group. All tests were 2-tailed, with a significance level set at *P*<.05.

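### The complete-case rule is tied to the whole week-8 assessment rather than to the outcome analysed, and it conflicts with the withdrawal rule, so the primary analysis set is not fixed

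*Protocol article*

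**What the plan says.** All references are to the protocol article.

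- **Data Analysis** sets the exclusion: "A complete case analysis was performed, excluding any participants with missing information on the posttraining assessment". For the missing-data check, baseline characteristics and scores "were compared between the complete data group and the missing data group". This is one split of the participants, not one per outcome. The primary model is an ANCOVA of change in knowledge score, with group as factor and baseline knowledge and years of psychotherapy experience as covariates. The secondary outcomes are handled in the same way.
- **Withdrawal From the Program** gives two other statements. Under intention to treat, "participants who did not respond to the 8-week posttraining assessment were retained in the analysis according to the group to which they were randomized". Then: "A complete case analysis was conducted, excluding any participants who withdrew at the posttraining assessment point".
- **Results** reports: "Due to withdrawals, incomplete surveys, and data loss, we had a total of 113 participants: 57 in the intervention group"; the remaining 56 were controls. It adds: "The amount of data varies for each measure". The Results paragraph of the Abstract says the same: "The amount of data varied across measures". Neither place gives counts per measure.

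**The concern.** The week-8 assessment has several parts: 17 knowledge items, 6 utilization items, 3 self-efficacy lines and 3 motivation lines. If completeness is judged over all of it, any of 6 + 3 + 3 = 12 answers that play no part in the primary outcome can remove a participant from the primary analysis. That discards primary-outcome data without any statistical reason.

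The second difficulty is that the article does not hold to one rule. Missing information, withdrawal and non-response are three different criteria, and the two Methods sections treat them differently. A reader cannot tell whether the primary ANCOVA has 113 participants or some other number, or who they are. This matters more because 47 of 160 participants are already missing from the final count, a larger share than the 25% attrition planned for.

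**Working it through.** **1. The statements side by side**

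| Participant at week 8 | Data Analysis, literal reading | Withdrawal From the Program |
|---|---|---|
| Withdrew | Out (no week-8 data) | Out |
| Did not respond, did not withdraw | Out | Retained |
| Knowledge answered, gap on another scale | Out | In (did not withdraw) |
| Everything answered | In | In |

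The sections disagree on the two middle rows. The second row has a further problem: the dependent variable is the change in knowledge, so a non-responder has no value to analyse in a complete-case model. The third row is the subject of this point.

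**2. Which reading of the Data Analysis rule does the text favour?**

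- For the whole-assessment reading: the participant is what is excluded, the assessment is named as a whole, there is a single complete-versus-missing split, and Results lists incomplete surveys, separately from withdrawals, among the reasons for the final count.
- For a per-outcome reading: the models are run one outcome at a time, and the amount of data is said to vary by measure. A set complete on the whole assessment would have one size for every outcome measured in both arms. Missing baseline scores do not obviously explain the variation, because the baseline questionnaires are reported for all 160 participants (Primary Outcome; text below Table 5).

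The text does not settle the matter.

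**3. The plan's own sample size**

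Inputs (Sample Size and Power Calculation; Data Analysis): f = 0.25, two-sided alpha 0.05, power 0.80, two groups, two covariates. Power comes from the noncentral F distribution with noncentrality f² × N, 1 numerator degree of freedom and N − 4 denominator degrees of freedom.

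At N = 128: 0.0625 × 128 = 8.0 with 124 degrees of freedom gives power 0.801. The stated 128 is reproduced.

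**4. Loss reported**

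160 − 113 = 47, and 47/160 = 29.4%.

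**5. What an outcome-specific rule could recover**

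The documents give no count of participants with knowledge data but gaps elsewhere. The values 5, 10 and 20 are assumptions, and zero is possible. I also assume that the primary analysis would otherwise have 113, and that the residual variance and the near-equal balance of arms are unchanged. The standard error then scales as √(113/N).

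| Recovered (assumed) | N | √(113/N) | Fall in standard error | Noncentrality 0.0625 × N | Power at f = 0.25 |
|---|---|---|---|---|---|
| 0 | 113 | 1.000 | 0% | 7.06 | 0.750 |
| 5 | 118 | 0.979 | about 2% | 7.38 | 0.768 |
| 10 | 123 | 0.958 | about 4% | 7.69 | 0.785 |
| 20 | 133 | 0.922 | about 8% | 8.31 | 0.816 |

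**6. Partly answered knowledge scale (a side issue)**

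The baseline alpha of 0.980 over 17 items implies a mean inter-item correlation r = 0.98/(17 − 16 × 0.98) = 0.742, if all items correlate equally. The variance of a mean of m items is proportional to r + (1 − r)/m: 0.758 for 17 items and 0.771 for 9. The part-whole correlation for 9 items is √(0.758/0.771) = 0.991. A mean of half the items would therefore be a close stand-in at baseline. Whether equal correlation holds after training on specific modules is not known.

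**The case against.** The strongest reply is that the rule was meant, and applied, within each model. Each ANCOVA would then drop only those lacking that outcome, and numbers would vary by measure, as reported. On that reading nobody with a knowledge score is lost and only the wording needs repair. This is a possible reading. It does not remove the point, because the literal wording and the single complete-versus-missing split lean the other way, and the conflict with Withdrawal From the Program remains.

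A reader might go further and infer that participants with usable knowledge data were in fact removed, and that the variation by measure proves the stated rule was not followed. The documents support neither inference:

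- The two do not sit together. If the rule was applied over the whole assessment, partial responders are lost but the numbers do not vary across the outcomes measured in both arms. If the numbers do vary there, the rule was probably not applied that way.
- Acceptability was measured only in the intervention group, so some variation arises by design.
- The Results sentences describe how much data there was. They are not an analysis rule, do not define the set in each model, and do not say that 113 is the fully complete set.
- Incomplete surveys are mentioned, but not how many there were or which questionnaire was affected.

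It is also tempting to say that the rule selects the most diligent responders. That is a plausible risk, but nothing in the article demonstrates it, and a baseline comparison of complete and missing groups is described.

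Finally, the lack of a rule for scoring a partly answered scale is not an error in the article. Such detail commonly sits in a full protocol or analysis plan that is not shown.

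**Conclusion.** The point holds as a defect in how the analysis set is fixed. The stated exclusion rule is not tied to the outcome, it contradicts the withdrawal section on non-responders and partial responders, and its literal reading fits poorly with data that vary by measure. This is more than missing detail, because the article states the rules and they disagree.

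The size is unknown and may be nil. Under the assumed recoveries of 5 to 20 participants, the gain is a 2% to 8% smaller standard error and a rise in power from 0.750 to between 0.768 and 0.816 at the planned effect size. These figures rest on 113 being the primary set under the current rule and on recovered participants having the same residual variance. The change should be made, but the article does not show that the primary result has been distorted.

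**What to change.** 1. In Data Analysis, define complete cases per outcome: a participant enters the ANCOVA for an outcome if that outcome was answered at baseline and at week 8, whatever is missing on the other scales.
2. Align Withdrawal From the Program with this rule, so that withdrawal, non-response and partial response are each treated in one way throughout.
3. Report the number analysed per arm for each outcome, and say how many of the 47 had incomplete surveys with knowledge data.
4. A half-items scoring rule (at least 9 of 17 for knowledge) is optional. If used, keep it to a sensitivity analysis.

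If the per-outcome rule is what was done, the cost is a change of wording and a table of counts. If it was not, the models must be re-run on whatever partial data survive; data loss is among the reasons given for the reduced count, so some may not. The numbers will differ between outcomes, which the article already accepts. Since analysis was completed in August 2024, a re-run is a post hoc change and should be labelled as such and shown beside the analysis already done.
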